| Serum pregnancy test (if indicated)                     | X             | X                           |                 |     |                  | D1                          |                 |     |                  | D1              | D1             |                            |
| PK d – phase I                               |               |                             |                 | D15 |                  | D1                          |                 | D15 |                  |                 |                |                            |
| Biomarkers i                                 |               | D1                          |                 |     |                  | D1                          |                 |     |                  | D1 e | D f |                            |
| Stool sample – phase II (optional) j         |               | D1                          |                 |     |                  |                             |                 |     |                  |                 |                |                            |
| Tumor biopsy (optional)                                 | X             |                             |                 |     |                  | D1                          |                 |     |                  |                 |                |                            |

a: differential WBC, haemoglobin, platelets (During treatment : D1, D8, D15 and D22 of cycle 1 and 2, and repeat before each Avelumab injection (ie. Day 1 and Day 15), at discontinuation visit and safety follow-up visit), aPTT, PT, INR (During treatment : D1, D15 of cycle 1 and 2, then D1 of each subsequent cycle, at discontinuation visit and safety follow-up visit)  
b: albumin, alkaline phosphatase, total bilirubin, urea, calcium, chloride, creatinine, creatinine clearance, glucose, LDH, phosphorus, potassium, total protein, SGOT [AST], SGPT [ALT], GGT, sodium, CPK, lipase, amylase (Screening, C1D1 and D15, C2D1 and D15, then D1 of each subsequent cycle, at discontinuation visit and safety follow-up visit)  
c: blood, glucose, protein, gravity (dipstick)  
d: all blood samples will be collected on pre-dose (1 point)  
e: D1C4, D1C6  
f: at progression  
g: only hepatic assessment (AST, ALT, alkaline phosphatase and GGT)  

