## 3.2. PHASE I – DOSE ESCALATION PART

### 3.2.1. Definitions

**Dose-limiting toxicity (DLT)** is defined as an adverse event or laboratory abnormality that fulfills all the criteria below:

- Begins on the first 28 days of treatment
- Is considered to be at least possibly related to the study treatment
- Meets one of the criteria below:
  - Hematotoxicity:
    - Persistent grade 4 neutropenia lasting  $\geq 7$  days;
    - When a neutrophil count of  $< 1000/\text{mm}^3$  and fever of  $\geq 38.0^\circ\text{C}$  is observed for  $> 2$  days;
    - Grade 4 thrombopenia or thrombopenia associated with a hemorrhage requiring platelet transfusion.
    - Grade 3 thrombocytopenia with bleeding.
  - Non-hematotoxicity:
    - $\geq$  Grade 3 non-hematotoxicities are considered as DLTs with the following specifications:
    - $\geq$  Grade 3 diarrhea, nausea, vomiting, and loss of appetite for  $\geq 5$  consecutive days (despite supportive therapy);
    - $\geq$  Grade 3 electrolyte imbalance for  $\geq 7$  consecutive days (despite supportive therapy);
    - Grade 3 dermatologic toxicity (Hand foot syndrome reaction and non-life threatening events) for  $\geq 7$  consecutive days;
    - Grade 4 dermatologic toxicity of any duration;
    - ALT/AST increases 5-8 X ULN with concomitant bilirubin increase  $< 2$  X ULN not resolving to  $< 5$  X ULN within 7 days
    - ALT/AST increases 5-8 X ULN with concomitant bilirubin increase  $> 2$  X ULN
    - ALT/AST increases  $> 8$  X ULN regardless of concomitant bilirubin increase
    - Bilirubin increase  $> 3$  X ULN not resolving to baseline within 7 days
    - $\geq$  Grade 3 immune-related adverse events lasting for  $\geq 8$  consecutive days despite steroid therapy.

In addition, the following will be considered as DLT:

- Any other study drug related AE considered significant enough to be qualified as DLT in the opinion of the investigators after discussion with the sponsor
- Any drug-related AE leading to Regorafenib or Avelumab relative dose intensity lower or equal to 75% over the first treatment cycle.

**Maximum tolerated dose (MTD):** is defined as the highest dose at which no more than 1 in 6 of the patients in the cohort experienced a DLT in the first treatment cycle.

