| 2. Laboratory tests*             | 
 
Hematology: neutrophils, lymphocytes, basophils, eosinophils, monocytes, haemoglobin, platelet count, red blood cell count, total white cell count.
 
                                                                                                   | Up to 24 hours before Day 1 of cycle 1
Repeat on Days 8, 15 and 22 of Cycles 1 and 2
Thereafter, repeat before each Avelumab injection (ie. Day 1 and Day 15).
At discontinuation visit                                                                                                                                                                                                                                             |
|                                         | 
 
Biochemistry: Serum electrolytes (Na+, K+, Cl, P and Ca++), liver function tests (AST, ALT, total bilirubin, GGT and AP), LDH, creatinine, glucose, total proteins, urea, albumin, CPK, lipase, amylase.
 
 | Up to 24 hours before Day 1 of cycle 1
Repeat on Day 15 of Cycle 1
Repeat before each Avelumab injection (ie. Day 1 and Day 15).
At discontinuation visit
Note that hepatic tests (AST, ALT, GGT and alkaline phosphatase) must be also performed at Days 8 and 22 of cycles 1 and 2                                                                                                                                      |
|                                         | 
 
Thyroid test: 
 
All cohorts : TSH,
 
For cohort F only : Thyroglobulin and Antithyroglobulin antibody
 
 
 
                                                                                         | Up to 24 hours before Day 1 of cycle 1 
 
All cohorts : TSH : Repeat on Day 15 of Cycle 1, repeat on Day 1 and Day 15 of cycle 2, then on Day 1 of each subsequent cycle, at discontinuation visit and safety follow-up visit
 
For cohort F only : Thyroglobulin and Antithyroglobulin antibody : repeat on Day 1 every 2 cycles, at discontinuation visit and safety follow-up visit
 
 |

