#### 11.4. EVENTS OF SPECIAL INTEREST

Potential drug-induced liver injury (DILI) are considered important medical events and should be reported as SAEs.

Patients with transaminase increase and/or alkaline phosphatase (AP)/gamma-glutamyl transpeptidase (GGT) increased with or without total bilirubin (TBIL) increase may be indicative of potential drug-induced liver injury (DILI).

The threshold for potential DILI may depend on the patient's baseline AST/ALT and TBIL values; patients meeting any of the following criteria will require further follow-up as outlined below:

- For patients with normal ALT and AST and TBIL value at baseline: AST or ALT > 3.0 x ULN and with TBIL > 2.0 x ULN
- For patients with elevated AST or ALT or TBIL value at baseline: AST or ALT > 2 x baseline and > 3.0 x ULN and TBIL > 2 x baseline and > 2.0 x ULN

Medical review needs to ensure that liver test elevations are not caused by cytolysis and/or cholestasis due to other causes, especially liver progression.

The evaluation should include laboratory tests, detailed history, physical assessment and the possibility of liver metastasis or new liver lesions, obstructions/compressions.

All cases confirmed with no other alternative cause for liver function test abnormalities identified should be reported as SAE. All events should be followed up with the outcome clearly documented.

For management of hepatic toxicity, refer to appendix 8.

For more information, refer to FDA's guidance document:

<https://www.fda.gov/downloads/Drugs/Guidance/UCM174090.pdf>.

Skin rash grade  $\geq 3$ , associated or not with fever, are considered important medical events and should be reported as SAEs (see section 11.3).

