| AST or ALT > 5 x ULN to ≤20 x ULN and/or total bilirubin > 3 x ULN to ≤ 10 x ULN            | 1st occurrence :
Interrupt Regorafenib treatment.
Monitor transaminases weekly until return to <3 times ULN or baseline.
Restart: If the potential benefit outweighs the risk of hepatotoxicity, decrease dose by one dose level, and monitor liver function weekly for at least 4 weeks.

Re-occurrence : Discontinue permanently | discontinue Avelumab therapy

Increase frequency of monitoring to every 1 to 2 days
1 to 2 mg/kg/day prednisolone or equivalent

Add prophylactic antibiotics for opportunistic infections
Consult gastroenterologist / hepatologist
Consider obtaining MRI/CT scan of liver and liver biopsy if clinically warranted

If returns to <3 times ULN or baseline:
Taper steroids over at least 1 month
If does not improve in > 3 to 5 days, worsens or rebounds: |
| >20 times ULN
or >3 times ULN with concurrent bilirubin > 2 times ULN                    | Any occurrence
Discontinue permanently
Monitor liver function weekly until resolution or return to baseline.                                                                                                                                                                                                                                | Add mycophenolate mofetil 1 gram (g) twice daily
If no response within an additional 3 to 5 days , consider other immunosuppressants per local guidelines
Re-occurrence : Discontinue permanently                                                                                                                                                                                                                                                                                         |

a For cohort [A], regorafenib should be interrupted and no dose reduction are allowed. Patients requiring a delay of > 4 weeks should permanently discontinue regorafenib

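### The Day 8 and Day 22 liver panel of cycles 1 and 2 omits total bilirubin, so the bilirubin-dependent DLT, DILI and Appendix 8 criteria cannot be assessed from those scheduled samples alone

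*Protocol*

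**What the plan says.** **Panel on Days 8 and 22.** Footnote g to the Synopsis schedule reads "g: only hepatic assessment (AST, ALT, alkaline phosphatase and GGT". The biochemistry row of section 5.5 agrees: "Note that hepatic tests (AST, ALT, GGT and alkaline phosphatase) must be also performed at Days 8 and 22 of cycles 1 and 2". Total bilirubin is in neither list. It belongs to the full biochemistry panel (footnote b and section 5.5), and section 5.5 counts it among the liver function tests.

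**Rules that use bilirubin.**
- Section 3.2.1, repeated in the Synopsis and section 9.1.1, has two DLT criteria of the form "ALT/AST increases 5-8 X ULN with concomitant bilirubin increase", split at a bilirubin of 2 x ULN. A third DLT criterion is a bilirubin above 3 x ULN that has not returned to baseline within 7 days.
- Section 11.4 defines potential DILI, for patients with normal baseline values, as "AST or ALT > 3.0 x ULN and with TBIL > 2.0 x ULN". The definition for patients with raised baseline values also needs bilirubin.
- The last row of the Appendix 8 liver table has the branch "or >3 times ULN with concurrent bilirubin > 2 times ULN". Two other rows can be entered on bilirubin alone.

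**Full panel from cycle 3.** Footnote b gives its timing as "Screening, C1D1 and D15, C2D1 and D15, then D1 of each subsequent cycle". The biochemistry row of the same table shows Day 1 and Day 15 for later cycles, and section 5.5 asks for biochemistry before every avelumab injection.

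**The concern.** The interim liver panel includes alkaline phosphatase and GGT, which none of these thresholds uses, and leaves out bilirubin, which several of them do. Day 22 is the only scheduled draw that lies after the first avelumab infusion and inside the 28-day DLT window. A patient whose bilirubin rises while transaminases stay low would pass that draw unnoticed. A patient with raised transaminases would have no same-day bilirubin, although that value decides between two DLT criteria, decides whether DILI is reported as an SAE, and decides which Appendix 8 row applies. Under section 4.1, patients with liver metastases may enter with AST or ALT up to 5 x ULN, so some already start in the range where bilirubin decides the Appendix 8 branch.

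**Working it through.** No sample size or error rate is involved. The check sets the scheduled draws against the rules.

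**Inputs.** 28-day cycles with C1D1 = day 1; first avelumab on C1D15 = day 15, with biochemistry drawn before it (section 5.5); DLT window days 1 to 28 (section 3.2.1); laboratory window of 72 hours (section 5.5).

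**Step 1: draws in cycles 1 and 2.**
- With transaminases: days 1, 8, 15, 22, 29, 36, 43, 50 = 8 draws.
- With bilirubin: days 1, 15, 29, 43 = 4 draws, each 14 days apart.
- Without bilirubin: 8 - 4 = 4 draws (days 8, 22, 36, 50).

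**Step 2: after the first infusion, inside the DLT window (days 16 to 28).**
- Draws with bilirubin: 0.
- Draws without bilirubin: 1 (day 22).
- C2D1 is nominally day 29. With 72 hours either way it falls on day 29 - 3 = 26 to 29 + 3 = 32, so it may land inside the window, but nothing requires it to.

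**Step 3: what a Day 8 or Day 22 sample can decide.**

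| Rule | Assessable from AST/ALT alone? |
|---|---|
| DLT: ALT/AST > 8 x ULN | Yes |
| DLT: ALT/AST 5-8 x ULN, bilirubin < 2 or > 2 x ULN (two criteria) | No |
| DLT: bilirubin > 3 x ULN, unresolved at 7 days | No |
| DILI, both definitions | No |
| Appendix 8: > 3 to 5 and > 5 to 20 x ULN rows | Yes for the transaminase trigger; no for the bilirubin trigger |
| Appendix 8: > 20 x ULN | Yes |
| Appendix 8: > 3 x ULN with bilirubin > 2 x ULN | No |

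So 3 of the 4 hepatic DLT criteria use bilirubin. Within 5-8 x ULN the doubt is narrower still. If transaminases have not fallen below 5 x ULN within 7 days, both branches give a DLT. If they have, the event is a DLT only if bilirubin exceeded 2 x ULN, and that value is not scheduled.

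**Step 4: with bilirubin on Days 8 and 22.** Bilirubin would fall on all 8 days, 7 days apart, with one value (day 22) after the first infusion and inside the DLT window.

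**Step 5: footnote b from cycle 3.** C3D1 is day 57 and C4D1 is day 85. Under footnote b the scheduled interval between full panels is 85 - 57 = 28 days. Under the schedule row and section 5.5 there is also a panel on day 71, so the interval is 14 days.

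**The case against.** The two descriptions of the Day 8 and Day 22 panel agree with each other, and the word only in footnote g suggests a deliberate interim check. That is fair: the mismatch is between the panel and the rules, not between two statements of the panel.

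A reader might infer that no scheduled test can trigger the hepatic rules after avelumab starts. The documents do not support this. ALT/AST above 8 x ULN is a DLT whatever the bilirubin. The joint rows of Appendix 8 and its > 20 x ULN branch respond to transaminases alone. Values of 3-5 x ULN raise no DLT question, because every transaminase DLT criterion starts at 5 x ULN.

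It might also be argued that a 14-day bilirubin interval makes the 7-day resolution criterion unobservable. That is too strong. Appendix 8 asks for monitoring every 3 days above 3 x ULN and every 1 to 2 days in the next row, which a bilirubin above 3 x ULN also enters. Since the protocol counts bilirubin among its liver function tests, that monitoring can be read as including it. What the schedule delays is the first detection.

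DILI and Appendix 8 are not confined to cycle 1, so the full panel at C2D1 can apply them about 7 days after Day 22.

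What remains is that the extra monitoring starts from an abnormal result that has been measured. It does not reveal an isolated bilirubin rise on a day when bilirubin is not tested, and it does not supply the value for the same sample.

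**Conclusion.** The point holds as a limited safety gap. In cycles 1 and 2, four of the eight scheduled transaminase draws carry no bilirubin, and on nominal days none is scheduled between C1D15 and C2D1. The main blind spot is an isolated bilirubin rise; the second is the missing same-day value when transaminases are raised. This rests on nominal visit days and on the schedule alone, without unscheduled tests.

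A reader might conclude that the recommended dose or the phase II efficacy results are compromised. The documents do not support that. Section 7.3 gives the phase II dose as already defined by phase I, so for DLTs the gap now bears only on how completely hepatic events were ascertained, and nothing shows that any were missed. No efficacy endpoint is affected. The live consequence is the timeliness of DILI recognition and of the Appendix 8 classification in the phase II cohorts, for which the Synopsis plans 735 patients.

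The footnote b conflict is a separate, smaller inconsistency. It would be wrong to infer that half of the infusions from cycle 3 will go ahead without liver tests: that would require a site to follow the footnote against both the table row and section 5.5.

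**What to change.** Reconcile the Day 8 and Day 22 panel with the rules that use bilirubin. One way is to add total bilirubin to footnote g and to the matching note in section 5.5. The cost is one more analyte on blood already drawn: four assays per patient at most, or 735 x 4 = 2,940 if every planned phase II patient completed both cycles. No visit, dose or stopping threshold changes. A reflex bilirubin only when transaminases are raised would supply the same-day value but would leave the isolated rise unseen.

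Separately, reconcile footnote b with the biochemistry row of the schedule and with section 5.5, so that the timing of the full panel from cycle 3 is stated in one way. This is a wording correction.

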## LIST OF ABBREVIATIONS AND DEFINITION OF TERMS

|                  |                                                                               |
|------------------|-------------------------------------------------------------------------------|
| AE (s)    | Adverse Event (s)                                                             |
| ALT       | Alanine Aminotransferase                                                      |
| ANC       | Absolute Neutrophil Count                                                     |
| ANSM      | Agence Nationale de sécurité du Médicament                                    |
| AP        | Alkaline Phosphatase                                                          |
| aPTT      | Activate Partial Prothrombin Time                                             |
| AST       | Aspartate Aminotransferase                                                    |
| AUC       | Area Under the Curve                                                          |
| BP        | Blood Pressure                                                                |
| BTC       | Biliary Tract Cancer                                                          |
| CI        | Confidence Interval                                                           |
| CNS       | Central Nervous System                                                        |
| CPK       | Creatine PhosphoKinase                                                        |
| CR        | Complete Response                                                             |
| CRC       | Colo Rectal Cancer                                                            |
| CRA       | Clinical Research Assistant                                                   |
| CrCL      | Creatinine Clearance                                                          |
| CRF       | Case Report Form                                                              |
| CRM       | Continual Reassessment Method                                                 |
| CT        | Computerized Tomography                                                       |
| DLT       | Dose Limiting Toxicity                                                        |
| DMP       | Data Management Plan                                                          |
| DQF       | Data Query Form                                                               |
| EC        | Ethic Committee                                                               |
| ECG       | Electrocardiogram                                                             |
| ECOG      | Eastern Cooperative Oncology Group                                            |
| EMA       | European Medicines Evaluation Agency                                          |
| FCPRCC    | Fédération des Comités de Patients pour la Recherche Clinique en Cancérologie |
| FFPE      | Formalin-Fixed Paraffin-Embedded                                              |
| FNCLCC    | Fédération Nationale des Centres de Lutte Contre le Cancer                    |
| FUP       | Follow-Up                                                                     |
| GEP-NETs  | Neuroendocrine gastroenteropancreatic tumors                                  |
| GCP       | Good Clinical Practice                                                        |
| GGT       | Gamma Glutyl-transferase                                                      |
| GIST      | Gastro Intestinal Stromal Tumor                                               |
| GMI       | Growth Modulation Index                                                       |
| HCC       | HepatoCellular Carcinoma                                                      |
| HCG       | Human Chorionic Gonadotropin                                                  |
| HIV       | Human Immunodeficiency Virus                                                  |
| IB        | Investigator Brochure                                                         |
| ICF       | Informed Consent Form                                                         |
| IDMC      | Independent Data Monitoring Committee                                         |
| IEC       | Institutional Ethics Committee                                                |
| IHC       | Immunohistochemistry                                                          |
| IMP       | Investigational Medical Product                                               |
| INR       | International Normalized Ratio                                                |
| IRB       | Institutional Review Board                                                    |
| IUD       | IntraUterine Device                                                           |
| IV        | Intravenous                                                                   |
| LDH       | Lactate Dehydrogenase                                                         |
| LFT       | Liver Function Test                                                           |
| MAD       | Maximum Administered Dose                                                     |
| MedDRA    | Medical Dictionary for Regulatory Activities                                  |
| MOA       | Mechanism Of Action                                                           |
| MRI       | Magnetic Resonance Imaging                                                    |
| MSI       | Micro Satellite Instability                                                   |
| MTD       | Maximum Tolerated Dose                                                        |
| NCI-CTCAE | National Cancer Institute Common Terminology Criteria for Adverse Events      |
| NPR       | Non Progression Rate                                                          |
| NSAIDs    | NonSteroidal Anti-Inflammatory Drugs                                          |
| NSCLC     | Non-Small Cell Lung Cancer                                                    |
| NYHA      | New York Heart Association                                                    |

|               |                                                                                |
|---------------|--------------------------------------------------------------------------------|
| ORR    | Objective Response Rate                                                        |
| OS     | Overall Survival                                                               |
| PD     | Progressive Disease                                                            |
| PDGFR  | Platelet-Derived Growth Factor Receptor                                        |
| PFS    | Progression Free Survival                                                      |
| PK     | Pharmacokinetic                                                                |
| PR     | Partial Response                                                               |
| PRE TT | Pre-Treatment                                                                  |
| PTT    | Prothrombin Time                                                               |
| RBC    | Red Blood Cell                                                                 |
| RECIST | Response Evaluation Criteria in Solid Tumors                                   |
| RR-DTC | Radioiodine-Refractory Differentiated Thyroid Cancer                           |
| RP2D   | Recommended Phase II Dose                                                      |
| RRePS  | Réseau de Référence en Pathologie des Sarcomes des Tissus mous et des Viscères |
| SAE    | Serious Adverse Event                                                          |
| SD     | Stable Disease                                                                 |
| SFUP   | Safety Follow-up                                                               |
| SmPC   | Summary Product Characteristic                                                 |
| SPC    | Summary of Product Characteristics                                             |
| STS    | Soft Tissue Sarcoma                                                            |
| SUSAR  | Suspected Unexpected Serious Adverse Reaction                                  |
| TAM    | Tumor Associated Macrophage                                                    |
| TLS    | Tertiary Lymphoid Structure                                                    |
| TME    | Tumor Micro-Environment                                                        |
| ULN    | Upper Limit of Normality                                                       |
| VEGFR  | Vascular Endothelial Growth Factor Receptors                                   |
| TT     | Treatment                                                                      |
| TSH    | Thyroid Stimulating Hormon                                                     |

